### Safety Analyses

The procedures related to this study do not modify the risks linked with any intracoronary procedure and a difference between the two groups is not expected. The following clinical events will be recorded, as they represent the standard clinical endpoints that are assessed to determine the safety and outcome after interventional procedures. All clinical data will be collected at discharge from hospital and during follow-up contacts at 3 and 12 months and will be evaluated by a data monitoring and safety board composed by physicians who are otherwise not involved in the study.

Periprocedural cardiac biomarker release is defined as (27):

In patients undergoing PCI with normal (≤ 99^th^ percentile URL) baseline cardiac troponin (cTn) concentrations, elevations of cTn >5 times the 99th percentile URL occurring within 48 h of the procedure.In patients undergoing PCI with elevated baseline, where two measures are available showing stable or falling values, a rise of >20% after PCI.In patients with elevated cTn levels before PCI and raising cTn or only one cTn value available, this endpoint cannot be evaluated.

Target lesion failure: defined as a composite of cardiovascular death, target-vessel myocardial infarction.

Target lesion revascularization: any (including attempted) repeat revascularization with either balloon angioplasty, stenting, or coronary artery bypass grafting, within the previous treated vessel segment including the 5 mm proximal or distal. Where there is doubt about the need for re-intervention, physicians are strongly recommended to use FFR of invasive imaging to ascertain whether re-intervention is required.

Death: Cause of death will be considered cardiac unless specified otherwise. In the primary analysis all deaths will be compared. The Coordinating site must be notified of a patient's death within 3 days of its knowledge. Data relating to the patient's death should be recorded. A copy of the death certificate with anonymized study identification number but with the patient's name removed should be sent to the coordinating site within 3 weeks of the patient's death. Post mortem results if available should follow as soon as possible.

Cardiac death: Any death due to proximate cardiac cause (e.g., MI, low-output failure, fatal arrhythmia), un-witnessed death and death of unknown cause, and all procedure-related deaths, including those related to concomitant treatment.

Vascular death: Death caused by non-coronary vascular causes, such as cerebrovascular disease, pulmonary embolism, ruptured aortic aneurysm, dissecting aneurysm, or other vascular diseases.

Non cardiovascular death: Any death not covered by the above definitions, such as death caused by infection, malignancy, sepsis, pulmonary causes, accident, suicide, or trauma.

Clinically relevant myocardial infarction: The Universal definition of Myocardial Infarction (Revision 2018) will be used to define clinically relevant myocardial infarction (MI) in this study (28).

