### Study Procedures

#### Consent and Randomization

Patients will be contacted after successful interventional treatment of the ACS, which includes treatment of all culprit lesions (typically >90% diameter stenosis or thrombotic lesions) and guideline-directed medical therapy. If all inclusion and no exclusion criteria are met, consent will be obtained. Prior to randomization, QFR will be measured in all participants in all coronary arteries presenting a lesion with 30–90% diameter stenosis. Patients with vessels with residual QFR <0.80 (residual QFR is the QFR calculated in the absence of the target lesion. A QFR <0.80 assumes that treatment of this/these focal lesion(s) would not remove the source of ischemia, such as in the case of diffuse disease) will be excluded. Thereafter, randomization will be performed in a 1:1 ratio with the use of randomly permuted blocks of 2, 4 or 6. The participants and treating physicians will be blinded to the treatment group allocation. Patients will be randomized to one of two strategies: angiography-guided (reference) or QFR-guided revascularization (experimental). In the reference arm, any decision regarding the treatment of non-culprit lesions will be based on the angiography performed at the time of the index PCI and the physicians will be kept blinded to the outcomes of QFR analysis. This strategy reflects the typical procedures used in daily routine; all lesions believed to be significant at angiography will be treated in one staged session. In patients randomized to QFR-guided revascularization, all lesions (one or more per vessel) associated with a vessel QFR <0.80 and a residual QFR >0.80 will be treated in one staged session (13). The treatment plan will be scheduled (according to angiography or QFR) by study investigators not involved in patient care. Only experienced medical staff, certified to use the software with the QFR system, will perform the measurements. Analyses will be conducted with QAngio XA 3D from Medis Medical Imaging Systems BV (Leiden, the Netherlands).

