**Table 2 T2:**
[figure not shown]
Study endpoints.

*Primary endpoint (clinical):* the primary endpoint (clinical) is a composite of patient-oriented events and significant angina (all-cause death, non-fatal myocardial infarction including type 1, 2, 4, unplanned hospitalization for angina or heart failure, unplanned revascularization, SAQ <90) at 12 months.

*Secondary endpoints:* the secondary endpoints include the following (at 3 and 12 months):

– the percentage of discordant results between functional (QFR ≤ 0.80) and angiographic coronary stenosis severity (diameter stenosis >70%).– the change in severity of angina pectoris as assessed by the SAQ summary score.– changes in the SAQ-7 domains (SAQ Physical limitation scale; SAQ angina stability scale; SAQ angina frequency scale; SAQ quality of life; SAQ Treatment Satisfaction).– incidence of a patient-oriented composite endpoint and its components (cardiovascular death, non-fatal myocardial infarction including peri-procedural, unplanned revascularization, unplanned hospitalization for angina, SAQ summary score <90) and its individual components.

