### Power Calculation

Functional endpoint: For the sample size calculation, the results of the FLOWER-MI trial will be used. In this study, which enrolled multivessel disease patients with at least one non-culprit lesion >50%, PCI was performed in 388 of 586 patients (66.2%) in the FFR-guided group and in 560 of 577 patients (97.1%) in the angiography-guided group; 366 of 826 (44.3%) lesions in the FFR group were reclassified from angiographically significant to non-significant based on FFR. Of note, although we allow patients with lesions >30% in our study, we foresee that [based on the results of the FLOWER-MI (10)], about 97% of the participants in our study will have at least one lesion >50%. Conservatively, we hypothesize a rate of decision to not perform PCI in our angiography group 4 times higher than that observed in the FLOWER-MI study (i.e., 13%). In the QFR group, we hypothesize a conservative decision in 33% (similar to that observed in the FLOWER-MI study). Based on this hypothesis, 176 patients are required to have a 90% chance of detecting, as significant at the 5% level, a decrease in the primary outcome measure from 33% in the QFR group to 13% in the angiography group.

Clinical endpoint: The clinical endpoint combines hard endpoints and angina: in the FORZA trial, comparing a FFR-guided with a OCT-guided PCI strategy, a composite of MACE + significant angina (all-cause death, non-fatal myocardial infarction, target vessel revascularization, SAQ <90) was taken. The incidence of this endpoint was 14.8% at 1 year in the FFR group (23). The incidence of the same endpoint in the FAME trial was 32.4% at 1 year in the angiography group (3). Given these assumptions, 176 patients are required for a power of 80% and an alpha error of 5% to observe a difference assuming an incidence of 14.8% in the QFR group and 32.4% in the angiography group.

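### Target lesion failure has no revascularisation term and target lesion revascularisation counts treated segments only, so neither records revascularisation of a deferred non-culprit lesion

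*Protocol article*

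**What the plan says.** All references are to the protocol article.

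- **Target lesion failure** (Safety Analyses): "Target lesion failure: defined as a composite of cardiovascular death, target-vessel myocardial infarction". No third component is printed.
- **Target lesion revascularisation (TLR)** (Safety Analyses, next item): any repeat revascularisation "within the previous treated vessel segment including the 5 mm proximal or distal".
- **Expected safety difference** (opening of Safety Analyses): study procedures leave the risks of intracoronary procedures unchanged, and "a difference between the two groups is not expected".
- **Other safety items**: for death, "In the primary analysis all deaths will be compared". For infarction, the 2018 Universal Definition "will be used to define clinically relevant myocardial infarction (MI) in this study". Neither is limited to a lesion or vessel. The safety board evaluates all clinical data from discharge and from the 3- and 12-month contacts.
- **Primary clinical endpoint** (Study Endpoints): "all-cause death, non-fatal myocardial infarction including type 1, 2, 4, unplanned hospitalization for angina or heart failure, unplanned revascularization, SAQ <90", at patient level. The secondary composite also contains unplanned revascularisation at any site, and its components are reported individually at 3 and 12 months.
- **Use of the term target lesion before treatment** (Consent and Randomization): "residual QFR is the QFR calculated in the absence of the target lesion". Here it means a lesion under assessment.
- **Planned deferral** (Power Calculation): "a decrease in the primary outcome measure from 33% in the QFR group to 13% in the angiography group", where the outcome is a decision not to perform PCI.

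**The concern.** The two strategies differ in which non-culprit lesions are stented and which are left alone. Lesion-level safety endpoints should therefore count a failed stent as a failure, and should show what happens at lesions left alone. The printed definitions do neither for revascularisation.

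The failure composite leaves out repeat revascularisation, so re-stenting without infarction does not count. TLR does count it, but only where a segment was treated before. By the plan's own assumption, more angiography patients than QFR patients have a treated non-culprit segment. TLR would then tend to come out lower with QFR even if lesions did equally well in both arms. A reader of the final report could take that for a safety advantage.

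The sentence that no difference between groups is expected makes this reading easier, because the functional endpoint is built on a difference in how many patients receive PCI.

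**Working it through.** **1. Which event counts where, as printed**

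| Event after randomisation | Target lesion failure | TLR | Patient-level endpoints |
|---|---|---|---|
| Treated segment re-stented, no infarction | No | Yes | Yes, if unplanned |
| Deferred non-culprit lesion stented later, no infarction | No | No (unless within the 5 mm margin of a treated segment) | Yes, if unplanned |
| Infarction from a deferred lesion | Only if its vessel is a target vessel (not defined) | No | Yes |
| Cardiovascular death from a deferred lesion | Yes | No | Yes |

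The first two rows are the defect. The third turns on a missing definition. If target vessel means a vessel with an assessed lesion, in line with the usage in Consent and Randomization, the infarction counts. If it means a treated vessel, it does not.

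**2. The plan's figure that uses the deferral rates**

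Inputs from Power Calculation: no PCI in 33% (QFR) and 13% (angiography), two-sided 5%, 90% power. The two-proportion formula with unpooled variance gives

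n per arm = (1.960 + 1.282)² × (0.33 × 0.67 + 0.13 × 0.87) / (0.33 − 0.13)² = 10.51 × 0.3342 / 0.04 = 87.8, rounded up to 88, so 176 in total.

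This matches the stated 176, so the rates below are the ones the plan works with.

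**3. Patients with a treated non-culprit segment, per 100 per arm**

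- QFR: 100 − 33 = 67
- Angiography: 100 − 13 = 87

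**4. Effect on TLR when true failure rates are equal (illustrative)**

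Suppose every patient with a treated non-culprit segment has the same TLR rate there, in either arm. For non-culprit segments alone:

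ratio = 0.67 / 0.87 = 0.77.

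Every enrolled patient also has a treated culprit lesion, and TLR as defined includes it. Let c be the culprit TLR rate per patient, relative to the rate per patient with a treated non-culprit segment. Then

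ratio = (c + 0.67) / (c + 0.87).

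| c | Ratio, QFR to angiography |
|---|---|
| 0 (culprit segments ignored) | 0.67 / 0.87 = 0.77 |
| 0.5 | 1.17 / 1.37 = 0.85 |
| 1 (equal contribution) | 1.67 / 1.87 = 0.89 |
| 2 | 2.67 / 2.87 = 0.93 |

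The documents give no value for c. On these assumptions the ratio is below 1 for any c, and its size shrinks as culprit segments contribute more. The calculation works per patient and takes no account of how many lesions each patient has treated or deferred.

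**The case against.** The strongest case on the other side is that nothing important is lost, and much of it stands.

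- **Failure is not confined to treated segments.** A reader might infer that both endpoints are unable to register harm at untreated lesions. The text does not support that for target lesion failure: cardiovascular death is tied to no lesion, and target-vessel infarction is defined by vessel. It is true only of revascularisation.
- **Overall harm is visible.** A reader might infer that the safety board sees failures only where a device was used. The text contradicts this. The board evaluates all clinical data. All deaths and any infarction under the Universal Definition are recorded, re-intervention and re-hospitalisation are collected at follow-up, unplanned revascularisation at any site is part of the primary and secondary composites, and a blinded committee adjudicates.
- **Deferral is not specific to QFR.** The plan expects it in 13% of the angiography arm, and expects QFR to add necessary procedures as well as prevent futile ones.
- **0.77 is not the effect on total TLR.** It leaves out the culprit segment that every patient has. Fewer stent failures after fewer stents is also a genuine result of the strategy, and it misleads only when TLR is read alone.
- **The endpoints are not central.** In the printed text neither one is named as primary or secondary (Table 2 is not shown). Lesion-level attribution of events may be set out in the full protocol or a committee charter.
- **The no-difference sentence can be read as risk per procedure.** That reading does not conflict with fewer procedures in one arm.

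None of this supplies the missing component of target lesion failure, settles the two uses of target lesion, or makes TLR comparable between arms as a lesion-level safety measure.

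**Conclusion.** The point holds as a defect in two stated safety definitions, not as a gap in the capture of harm. As printed, a treated lesion revascularised without infarction is not a target lesion failure, and a deferred lesion revascularised later is not a TLR. The missing term may be an editorial slip, since the list has no closing conjunction and TLR follows directly, but followed literally it changes what is counted.

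Under the planned deferral rates, with equal failure rates in the two arms, TLR at non-culprit segments would be lower with QFR by a factor of about 0.77. With an equal contribution from culprit segments, total TLR would be lower by a factor of about 0.89. These figures illustrate the direction and order of the effect and are not predictions. Patient-level endpoints keep total harm in view but, as described, do not say whether an event arose at a culprit, treated non-culprit or deferred lesion. No primary or secondary conclusion in the printed text rests on the two definitions. What is at stake is how the lesion-level safety results will be read.

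**What to change.** 1. Add TLR to the target lesion failure composite.
2. Keep culprit and treated non-culprit segments in TLR. Narrowing the target lesion to the non-culprit lesions in which QFR was measured would drop failures of culprit stents.
3. Define target lesion and target vessel once, and make the definitions consistent with the usage in Consent and Randomization.
4. Add a separate safety item, reported by arm: infarction or unplanned revascularisation at a deferred non-culprit lesion. The existing blinded events committee can attribute these events, with an undetermined category.
5. Reword "a difference between the two groups is not expected" so that it refers to risk per procedure, and state that exposure to PCI is expected to differ between arms.

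The cost is some definition wording and one extra adjudication field. QFR is already measured before randomisation in every artery with a 30–90% lesion, so the assessed arteries are on record. The downside is small: some infarctions cannot be attributed to a lesion and will be classed as undetermined.

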### Confidentiality

Patient data will be pseudonymized and collected by the study team. Pseudonymized patient data will be stored digitally and only accessible to the members of the study team. After 10 years of storage, the data will be destroyed. It is not intended to give study participants' data to a third party. All data will be analyzed after the last patient is discharged from index hospitalization. No interim analysis is intended except for the safety evaluation performed by the Data Safety Monitoring Board consisting of two physicians not affiliated with the study. In case a study participant withdraws consent after having his data collected from him, the patient's data will be anonymized.

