#### Staged Revascularization

Staged PCI will be performed 4 weeks after the first PCI performed in the setting of the ACS. PCI will be performed with newer-generation drug eluting stents at the operator's discretion. Use of intracoronary imaging is allowed, but not for the assessment of the relevance of the stenosis (i.e., not for overruling the decision made by angiography or QFR). FFR or other invasive hemodynamic assessments prior to PCI are not allowed.

Reference vessel diameters calculated by the QFR software will be used.

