#### SAQ Questionnaires

The first SAQ questionnaire will be administered before the staged revascularization, i.e., ~4 weeks after the ACS event. The SAQ-7 provides a quantitative analysis of 5 domains (physical limitation, angina stability, frequency, treatment satisfaction, and quality of life) reflecting the impact of angina on patients' health status during the previous 4 weeks. Scores for each domain go from 0 to 100, with 100 defining absence of limitations. The SAQ score at 1 month after ACS correlates with the subsequent incidence of mortality, hospitalization, and resource use (22). The SAQ-7, along with clinical follow-up data (death, re-hospitalization, re-intervention) will be collected at 3 and 12 months after protocol-mandated complete revascularization during office or telephone visits.

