### Ethics and Publication Policy

The protocol has been approved by the local state medical association's ethics committee. The procedures outlined in this protocol for the conduct, evaluation and documentation of this study are intended to ensure that all persons involved in the study comply with GCP and the ethical principles described in the Declaration of Helsinki. The study will be conducted in accordance with local legal and regulatory requirements. The requirements of the German Medicines Law, the GCP regulation and the Federal Data Protection Law are adhered to.

The PI of this study is committed to the unrestricted and widespread dissemination of all primary and secondary endpoint results and tertiary analyses. At the conclusion of the study, an abstract reporting the primary results will be prepared by the investigators and presented. A publication will similarly be prepared for publication in a reputable scientific journal. No outcome data from either endpoint will be published or made available to the Investigators in any form, unless decided otherwise from the data safety and monitoring board, until the discharge of the last patient enrolled into the study. Following analysis and presentation of the primary endpoint results, active participation of all study group members will be solicited for data analysis and abstract and manuscript preparation and therefore included as co-authors. Submission of all abstracts and publications regarding the primary endpoint and secondary endpoints from the study requires approval by the PI after review by all members of the study group.

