### Trial Status

Data collection is ongoing. The first patient was enrolled in October 2020. We expect the study to be completed in May 2022.

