Our study has several limitations. First, the study population is relatively small and the study is not designed to test hard clinical endpoints. Second, the presence of diffuse spasm at the time of an ACS might lead to an overestimation of non-culprit lesions in both groups. In a recent study by Sejr-Hansen et al., QFR performed in the setting of a ACS showed however a very good correlation with staged QFR and also a good diagnostic performance as compared to staged FFR (38). Based on these data, QFR performed in the acute setting appears to maintain its clinical validity. Third, the primary endpoint is assessed at 12 months after protocol-mandated complete revascularization; complaints due to myocardial ischemia, which may occur after a period of more than 1 year, will not be recorded. However, data from the ischemia trial appear to suggest that the incidence of angina remains constant during longer follow-up periods (39).

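### The stated time for analysing and releasing all data allows the clinical and SAQ endpoints to be analysed about 12 to 13 months before the last patient's 12-month assessment

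*Protocol article*

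**What the plan says.** **Time of analysis.** Confidentiality: "All data will be analyzed after the last patient is discharged from index hospitalization". The next sentence rules out any interim analysis other than the safety evaluation by the data safety monitoring board.

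**Release of outcome data.** Ethics and Publication Policy: data from either endpoint are neither published nor given to the investigators "until the discharge of the last patient enrolled into the study", unless the board decides otherwise. The same section places the abstract with the primary results at the end of the study.

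**Endpoint timing.** Study Endpoints: the primary clinical endpoint is a composite that ends with "unplanned hospitalization for angina or heart failure, unplanned revascularization, SAQ <90) at 12 months". SAQ Questionnaires: the SAQ-7 and clinical follow-up data "will be collected at 3 and 12 months after protocol-mandated complete revascularization during office or telephone visits". The limitations paragraph of the Discussion repeats that "the primary endpoint is assessed at 12 months after protocol-mandated complete revascularization".

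**Interval before follow-up starts.** Staged Revascularization: "Staged PCI will be performed 4 weeks after the first PCI performed in the setting of the ACS". SAQ Questionnaires: "The first SAQ questionnaire will be administered before the staged revascularization, i.e., ~4 weeks after the ACS event".

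**Primary analysis population.** Statistics: the modified intention-to-treat (mITT) set is limited to randomized patients who have a 12-month assessment of the primary endpoint variable.

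**Calendar.** Trial Status: "The first patient was enrolled in October 2020. We expect the study to be completed in May 2022".

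**The concern.** The analysis sentence covers all data, yet it is anchored to a hospital stay that ends before the last patient has had a baseline SAQ, a staged procedure or any follow-up contact. Nothing in the article ties the analysis, or access to the data, to completed 12-month follow-up.

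If the earliest permitted date were used, three things would follow.

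- **Selection by enrolment date.** Patients still in follow-up would have no 12-month assessment, so the mITT rule would exclude them. The clinical endpoint would rest on early enrollees only.
- **An unplanned look.** A comparative analysis of partial 12-month data would in effect be an interim analysis, which the same section says is not intended.
- **Knowledge of results during follow-up.** Investigators could see comparative results while SAQ scores, hospitalization for angina and unplanned revascularization are still accruing. These components are patient-reported or depend on clinical decisions, so they are the ones most open to influence.

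**Working it through.** The plan states no figure for the gap between analysis and endpoint, so there is none to reproduce. The sample sizes are not at issue here.

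**Inputs**

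| Input | Value | Source |
|---|---|---|
| First PCI to staged PCI | 28 days | Staged Revascularization |
| Staged PCI to clinical endpoint | 12 months | SAQ Questionnaires; Discussion |
| Index stay | not given; 3 to 14 days assumed | assumption |
| First enrolment; expected completion | October 2020; May 2022 | Trial Status |

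One month is taken as 30.4375 days.

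**Step 1. First PCI to 12-month assessment, patient with staged PCI.**
28 / 30.4375 + 12 = 0.92 + 12 = 12.92 months.

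**Step 2. Index discharge to 12-month assessment.** Gap = 12.92 − stay.
- 3-day stay: 12.92 − 3/30.4375 = 12.92 − 0.10 = 12.82 months.
- 14-day stay: 12.92 − 14/30.4375 = 12.92 − 0.46 = 12.46 months.

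**Step 3. Patient assigned to medical treatment.** There is no staged PCI, and the article does not say where the 12 months start. If they start at the index event, the gap is 12 − 0.10 = 11.90 months to 12 − 0.46 = 11.54 months.

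The gap is therefore about 12 to 13 months, whichever origin applies.

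**Step 4. What exists for the last patient at index discharge.** The first SAQ comes about 4 weeks after the ACS, so under the assumed stay it is missing. The 3-month contact falls 0.92 + 3 = 3.92 months after the first PCI, so it is missing too. Treatment assignment, which is the functional endpoint, can be known at or soon after discharge.

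**Step 5. The meaning of discharge in the publication section.** That sentence does not name the index stay.
- Index stay: the gap is as in Steps 2 and 3.
- Stay for the staged procedure: the gap is still about 12 months.
- Leaving the study after follow-up: there is no conflict, but the text does not say this.

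**Step 6. The calendar.** October 2020 to May 2022 is 18 to 20 months, depending on the days.
- If May 2022 includes 12-month follow-up, enrolment lasts about 18.0 − 12.9 = 5 months to 19.9 − 12.9 = 7 months. At the last index discharge no patient would have reached 12 months.
- If May 2022 is the end of enrolment, and accrual is uniform over 19 months, (19 − 12.92) / 19 = 32% would have reached 12 months.

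The article states neither the meaning of the date nor the accrual pattern. Step 6 shows only how far the outcome depends on them.

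**The case against.** The strongest reply is that the two sentences set earliest dates. The first says *after* and the second says *until*; neither orders an analysis or a release on the day of discharge. An analysis after full 12-month follow-up would comply with both. The rest of the article points that way: the endpoint, the mITT definition and the follow-up contacts are all set at 12 months, and the primary results are to be reported when the study concludes. Participants, treating physicians and the events committee are blinded, which narrows the route by which a leak could affect outcomes. For the functional endpoint the stated time is suitable.

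Most of this stands, and it limits the point. A reader might infer that the plan requires analysis at the last index discharge, that a second unplanned analysis is inevitable, or that May 2022 is wrong. The documents support none of these. Waiting is allowed, and no accrual rate is given against which the date could be tested. Nor can one say how many patients would lack the endpoint: the 0% and 32% in the calendar check rest on assumptions about accrual and about what completion means.

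The reply does not remove the conflict. The analysis sentence is the only time of analysis given, it covers all data, and an earliest date that precedes the endpoint by about a year gives that endpoint no protection. The release sentence covers either endpoint, so it cannot be read as confined to the functional one.

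**Conclusion.** The point holds as an internal inconsistency about when clinical and SAQ data may be analysed and released. The stated earliest time of analysis precedes the last patient's 12-month assessment by about 12.5 to 12.8 months after staged PCI, and by about 11.5 to 11.9 months for a medically treated patient counted from the index event. These ranges assume an index stay of 3 to 14 days. The conflict itself does not depend on that assumption or on any accrual pattern.

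It reaches the primary clinical endpoint and the 3- and 12-month clinical and SAQ endpoints. It does not reach the functional endpoint. The loss of late enrollees from the mITT set and the early sight of results are conditional: they arise only if the earliest permitted date is used. For the release sentence, the conflict also depends on discharge meaning a hospital stay and not exit from the study, which the text leaves open.

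**What to change.** Amend the Confidentiality and the Ethics and Publication Policy sections to say the following: comparative analysis of the clinical and SAQ endpoints, and release of those data to investigators, take place only after the last randomized patient has completed the 12-month assessment, or has died or withdrawn, and the database is locked. Any earlier analysis is limited to the functional endpoint, with clinical and SAQ data kept masked.

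In Trial Status, state whether May 2022 means the end of enrolment or the end of follow-up.

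The cost is a few sentences of wording and possibly a later reporting date. No extra patients, visits or procedures are needed.
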